### Data Collection and Measures

#### Primary Outcomes

Led by the values they identified as guiding the study (Figure 1), the Steering Committee sought to emphasize children’s relationship with the land and care for the environment. Thus, study outcomes were prioritized to understand how the PRO-ECO project influenced children’s engagement with the land. As a result, the primary outcome chosen for the PRO-ECO 2.0 study was the occurrence of outdoor nature play behavior at ELCC centers. While the primary study outcome differs from the PRO-ECO 1.0 study, where the occurrence of play versus nonplay was assessed, children’s outdoor play behavior was still coded using the expanded version of the Tool for Observing Play Outdoors (TOPO) [42]. The TOPO is designed to measure 8 play types (physical play, exploratory play, imaginative play, play with rules, bio play, expressive play, restorative play, and digital play) and one nonplay type, along with corresponding subtypes. For this study, we coded nature play behavior through the TOPO bio play behavior type, which includes subtypes for play (observing; discussing; or interacting with plants, wildlife, or natural materials, as well as playing in a way that demonstrates care or stewardship of the environment or appreciation of nature). To further refine observed nature play behavior, children’s environmental interactions (loose parts, fixed parts, natural elements, manufactured elements) were also recorded and coded.

The TOPO was implemented through a child-based, observational behavior mapping (OBM) protocol. The purpose of OBM is to understand how an environment supports movement and play behavior by mapping, recording, organizing, and analyzing geographically located data (37). Base maps were developed for each center and uploaded onto digital tablets to facilitate geo-located coding of play behavior. Due to the rural locations and varied geographic distances of most participating ELCC centers, the research team did not code play behavior in situ as was done in the PRO-ECO 1.0 study. Further, in situ coding requires significantly more time, and obtaining reliability in coding requires extensive training, making it unfeasible to have ELCC staff code the play behavior directly on-site. As a result, the liaisons at each center were trained to observe and video record children while outside during scheduled outdoor time. Children were recorded according to a systematic protocol where the liaisons at each ELCC center had a list of consented children. They then captured a 2-minute video of the child’s outdoor play and verbally dictated what they noticed about the play during the video observation. We aimed to collect a total of 64 two-minute videos for each ELCC center at each data collection time point (time 1, time 2, and time 3). The observational data were collected at the child level, where individual children were the unit of observation and observations aimed to capture all consenting children. This differs from the PRO-ECO 1.0 study, which collected observational data at the center level to study children’s outdoor play in connection to their ELCC. Following the collection of videos at each time point, research staff split each 2-minute video into 15-second clips (512 video clips at each center for each time point). Trained and reliable coders coded each 15-second clip to assess the TOPO play types and subtypes. The reliability of the OBM method is defined by the degree of interrater reliability and interrater agreement, which was assessed using weighted κ and intraclass correlation coefficients [43,44]. κ Values of ≥0.70 are commonly accepted as adequate for scientific research [43]. A κ value of 0.82 was achieved between coders in relation to the primary outcome variable (TOPO) prior to beginning video coding.

Additional variables were collected through the OBM protocol in this study, including risk-taking behavior, activity intensity, peer interaction, adult interaction, and play communication. Further details on the OBM protocol and process are available in the PRO-ECO 1.0 study protocol by Ramsden et al [22].

#### Additional Outcome Measures

##### ECE Attitudes Toward Outdoor Risky Play

To understand how ECEs’ attitudes toward outdoor risky play may shift over the course of the study, we measured educator perspectives using the Teacher Tolerance of Risk in Play Scale (T-TRiPS) [45]. The T-TRiPS is a 25-item instrument and has been validated for use as a measure of intervention effects aimed at increasing children’s access to risky play (a fundamental component of outdoor play). Questions include items that range from those that most ECEs should have little trouble endorsing (eg, “Do you let children in your center play chase with one another”) to those that they might find more challenging (eg, “Do you let children in your center use adult tools [eg, hammer and nails, knife, scissors] unsupervised?”), with the response options being “yes” or “no.” ECE’s at participating ELCC centers completed the T-TRiPS at time 1 and time 3.

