**Methods:**

This study considered a 5 R’s research approach from its inception, beginning with the formation of a Steering Committee and over a year of relationship building before formal study activities commenced. A key early focus was collaboratively identifying project values through an iterative process. Collectively, we worked to promote equity, disrupt power dynamics, and embed Indigenous data sovereignty principles into research agreements, marking a significant departure from traditional Western research processes. The PRO-ECO program and study protocol are implemented in partnership with 10 ELCC centers delivering licensed full-day, year-round care to children aged 2.5-6 years in rural and urban areas of British Columbia, Canada. The PRO-ECO program includes 4 components to address common barriers to outdoor play in ELCC settings. Primary outcome measures include the proportion and diversity of observed nature play behavior during dedicated outdoor times at ELCC centers as measured through observational behavior mapping. Secondary outcomes include changes in educator attitudes, quality of ELCC outdoor play space, and children’s perspectives of their experiences at ELCC centers. Outcome data are collected at baseline, and 6 months and 12 months post baseline. The community’s perspectives (educators, children, and families) on the project are assessed qualitatively to understand the acceptability of the PRO-ECO program. Mixed-effect models will test the effect of the PRO-ECO program on quantitative outcomes. Qualitative data will support the interpretation of quantitative findings and provide evidence on project acceptability.

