### Randomization

Individual ELCC centers served as the unit of randomization in the waitlist control cluster randomized trial design. ELCC centers were randomized to either group 1 or group 2 prior to baseline data collection. Five group 1 centers implemented the PRO-ECO program immediately following baseline data collection, whereas 5 group 2 centers, acting as waitlist control sites, implemented the PRO-ECO program following time 2 data collection. Randomization was conducted by Steering Committee members who randomly drew 5 separate slips of paper with ELCC center names to represent group 1. The research trial coordinator was not blinded to the randomization, and ELCC centers were aware of their group during baseline data collection because planning was already underway with group 1 ELCC centers for launching the implementation of the PRO-ECO project. Data on outcome measures were collected at 3 time points: baseline (time 1), 6-month follow-up (time 2), and 12-month follow-up (time 3). Outcome data aimed to assess the short-term and longer-term outcomes within group 1 and the short-term outcomes within group 2. Data collection occurred during the fall and spring seasons to compare similar weather patterns at each data collection time point.

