##### Quality of ELCC Outdoor Spaces

Modifications to the outdoor environment were guided by the Seven Cs design guidelines [40]. A simplified version of the Seven C’s was developed by the research team, as seen in Table 3, in order to facilitate its completion by ELCC staff. At time 1 and time 3, center staff were encouraged to complete the Seven Cs together, centering the perspective of the children at their center. In addition to acting as a baseline measure, the time 1 measurement provided guidance to the centers regarding elements of the outdoor environment that are working well and those that might require improvements. Subsequent measurements indicated how the modifications impacted the quality of the ELCC outdoor spaces.

**Table 3 table3:** Seven Cs characteristics and ratings adapted from Herrington and Lesmeister [40] and Brussoni et al [46].

Characteristic	Rating (5=strongly agree, this is well done in my center; 4=somewhat agree; 3=neutral; 2=somewhat disagree; 1=strongly disagree, this is lacking in my center)
Character	The entire space feels welcoming for the children and ECE (eg, soft materials, dappled light, some color)
Context	The property or area beyond the play space fence contributes positively to the atmosphere of the play space
Connectivity	The children can move seamlessly from one area of the yard to another (eg, defined pathways for tricycles, and pathways for foot traffic only, such as stepping stones or tree cookie paths)
Clarity	Different zones of play are clearly identifiable at the child’s height (eg, messy zones, sand play, water play, tricycle space)
Chance	Throughout the play space, there are natural and loose materials to create and build with, manipulate, and move with
Change	There are ample amounts of natural features, such as trees, shrubs, and groundcovers, in the play space (or directly adjacent to the play space) that change with the seasons
Challenge	The play space encourages different levels of physical and cognitive risk-taking (eg, height, speed, using tools, hiding/getting lost, rough-and-tumble)?

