Baseline demographic and ELCC characteristics will be summarized by group using means and SDs, medians and IQRs for continuous variables, and frequencies and percentages for categorical characteristics. Bivariable relationships between children’s demographic characteristics and outdoor nature play occurrence, both overall and by group, will be explored to identify potential confounding factors at the individual level, considering randomization occurs at the cluster level. Mixed effects models will be used to assess differences in quantitative outcome measures between groups, as well as within-group comparisons of pre- and postprogram implementation measures.

We will analyze child interviews using qualitative content analysis methods to systematically identify patterns and themes that reflect children’s perspectives and experiences on outdoor play and well-being [51]. The method’s adaptability to diverse data types and research contexts, combined with its structured and systematic analytical process, makes it particularly viable for exploring the wide-ranging and expressive nature of children’s responses. For ECE and family listening circles and interviews, we will use thematic analysis, which involves identifying and analyzing key themes within the data [52]. We will follow a reflexive thematic analysis to facilitate insights regarding ECEs’ and families’ perspectives on various interconnected topics, such as the importance of outdoor play, power dynamics, cultural norms on outdoor play, and the acceptability of the PRO-ECO program.

In alignment with the PRO-ECO project values and the partner research agreements, we will work with participating ELCC centers and the Steering Committee to share ongoing results from this study. Steering Committee members and liaisons will be invited to join a working group to work with the Outside Play Lab team on guiding and interpreting the analyses. We will gather ongoing iterative input from the broader Steering Committee and ELCC center teams to help interpret the findings, guide subsequent analyses, and develop recommendations. This form of member checking will seek to ensure all analyses and results align with the desired outputs of our project partners and appropriately convey the findings.

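### T-TRiPS and Seven Cs are measured only before either group starts the program and after both were scheduled to have had it, so they cannot support a controlled test of the program effect

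*Protocol article*

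**What the plan says.** All from the protocol article.

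- **Measurement times.** Under ECE Attitudes Toward Outdoor Risky Play, educators at "participating ELCC centers completed the T-TRiPS at time 1 and time 3". Under Quality of ELCC Outdoor Spaces: "At time 1 and time 3, center staff were encouraged to complete the Seven Cs together". Neither section mentions time 2.
- **Program start.** Under Randomization, the five centers of group 1 begin as soon as their baseline measurements are done. For the remaining centers the section says: "5 group 2 centers, acting as waitlist control sites, implemented the PRO-ECO program following time 2 data collection". The Results section dates the programs to December 2023 to April 2024 for group 1 and May to September 2024 for group 2.
- **Claims.** The abstract lists educator attitudes and outdoor-space quality among the secondary outcomes. It says, without exception, that outcome data come from baseline, 6 months and 12 months, and then: "Mixed-effect models will test the effect of the PRO-ECO program on quantitative outcomes". Data Analysis says: "Mixed effects models will be used to assess differences in quantitative outcome measures between groups". The same sentence adds within-group comparisons before and after the program. The Seven Cs section treats later ratings as showing what the modifications did to the quality of the space.

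**The concern.** A waitlist design gives a controlled estimate only while one group has the program and the other is still waiting. Here that window closes at time 2. An outcome skipped at time 2 loses the comparison for which the centers were randomized.

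Two misreadings follow if the text is applied as it stands. A between-group test on the time 1 to time 3 change could come out null although the program works, and be reported as no effect on attitudes or space quality. Or a within-group gain could be reported as a program effect although nothing separates it from twelve months of other change.

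The second risk is sharper for the Seven Cs. Centers knew their group during baseline data collection, and their staff designed the modifications. The liaisons attended a workshop on the same guidelines, and the time 1 ratings told centers what to improve. The staff then rated their own space.

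**Working it through.** **The plan's own figure.** No power or sample size is given for these two outcomes. The only power figure, 0.997, concerns the clip-level primary outcome. Its effect size follows from its inputs (0.00295 / 0.958 = 0.00308). With alpha 0.05 (assumed, as none is stated), the F test for one added predictor among six gives power 0.978 at N = 5,120 and 1.000 at N = 15,360. This is consistent with the stated figure but has no bearing on this point.

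**Step 1: program status at each time, from the Randomization section.**

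| | Time 1 | Time 2 | Time 3 |
|---|---|---|---|
| Group 1 | 0 | 1 | 1 |
| Group 2 | 0 | 0 | 1 |
| T-TRiPS, Seven Cs measured | yes | no | yes |

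The groups differ only in the time 2 column.

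**Step 2: what each contrast estimates.** Let τ be the change from time 1 to time 3 that would occur without the program, δ_S the effect soon after the program, and δ_L the effect at longer follow-up.

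- Group 1 change = τ + δ_L
- Group 2 change = τ + δ_S
- Between-group difference = δ_L − δ_S: τ cancels, and what remains is earlier versus later start. It is 0 when δ_L = δ_S, however large both are.
- Within-group change = τ + δ: the two parts cannot be separated.

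Had time 2 been measured, and with τ₂ the time 1 to time 2 change without the program, the between-group difference would be (τ₂ + δ_S) − τ₂ = δ_S.

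**Step 3: identification.** Model: intercept, group, time, program indicator.

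| Times used | Columns | Rank | Rank without program column | Program effect identified |
|---|---|---|---|---|
| 1 and 3 | 4 | 3 | 3 | no |
| 1 and 2 | 4 | 4 | 3 | yes |
| 1, 2 and 3 | 5 | 5 | 4 | yes |

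This needs no assumed SD, effect or alpha.

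**Step 4: illustration.** Center-level changes, 5 versus 5 centers, 20,000 runs. Assumptions, none from the article: SD of change 0.5, two-sided alpha 0.05, and the same program effect δ in both groups. Entries are rejection rates.

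| δ | τ | Between groups, T1–T3 | Pre/post, both groups pooled | Between groups, T1–T2 (not collected) |
|---|---|---|---|---|
| 0 | 0 | 0.050 | 0.049 | 0.045 |
| 0 | 0.5 | 0.048 | 0.804 | 0.050 |
| 0.5 | 0 | 0.050 | 0.801 | 0.290 |
| 0.5 | 0.5 | 0.050 | 1.000 | 0.287 |
| 1.0 | 0 | 0.047 | 1.000 | 0.790 |

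The T1–T3 between-group test stays near 5% whatever δ is. The pre/post test rejects about 80% of the time both for a background shift of 0.5 with no program effect and for a program effect of 0.5 with no shift. The rates in the last two columns depend on the assumed SD. The near-5% rate in the T1–T3 column depends on equal gains.

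**The case against.** The best defense is that the article asks little of these outcomes. T-TRiPS is listed as an additional measure, meant to show how attitudes may shift during the study, and the abstract speaks of changes in attitudes. The within-group comparison is already planned and the data can supply it. The sentences on testing an effect and comparing groups cover all quantitative outcomes together, including the primary one, and outcome-specific models may be left to an analysis plan. All of this stands as a description of tone. It does not rescue the general sentences, which make no exception, or the Seven Cs sentence, which is specific and causal. No analysis plan can restore a measurement that was not taken.

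A reader might infer that randomization contributes nothing to these outcomes. The documents do not support that. The T1–T3 group contrast is still a randomized comparison of earlier with later start, and Randomization states an interest in longer-term outcomes in group 1 and short-term outcomes in group 2. What is absent is the comparison of program with no program.

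A reader might also infer that a null between-group result is certain. It is expected only if both groups gain equally by time 3. The Discussion says implementation overran in some centers, so exposure at time 3 may be uneven. That variation was unplanned and not randomized, and does not recreate a control group.

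Finally, one joint Seven Cs rating per center, hence 5 per group at each time, is implied by the instruction to complete it together but not stated.

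**Conclusion.** The point holds for T-TRiPS and the Seven Cs. Their data contain no program-versus-no-program contrast, and this follows from the schedule alone. The between-group change estimates earlier versus later start; the within-group change is uncontrolled and rated by unblinded staff. The claims about three collection times, a test of the program effect, and the impact of the modifications therefore do not hold for these two outcomes.

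The approximately 5% rejection rate rests on equal gains by time 3 and an assumed alpha of 0.05. The 80% figures also rest on an assumed SD of change of 0.5.

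It would go too far to treat this as a flaw in the trial's main result: the article aims to collect play videos at all three times, so the primary outcome keeps its time 2 contrast. Because two secondary outcomes are affected and the remedy is wording, this is something that should be fixed before results are reported, not an obstacle to the main analysis.

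**What to change.** 1. In the abstract, limit the statement about testing the program effect to outcomes measured at time 2, and say that T-TRiPS and the Seven Cs were collected at time 1 and time 3 only. Make the same exception where Randomization lists three time points for outcome measures.
2. In Data Analysis, present both outcomes as uncontrolled time 1 to time 3 change. Give intervals that respect clustering in 10 centers with a small-sample correction, since standard cluster methods are unreliable with so few clusters.
3. State that any group difference at time 3 is read only as earlier versus later start, and that a null there is not evidence against the program.
4. In the Seven Cs section, replace the causal reading with a description of how ratings changed, and note that unblinded staff rated their own space.

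The cost is weaker claims for two secondary outcomes. Data collection ended in March 2025, so no time 2 measurement can be added. The primary analysis does not change.

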##### Quality of ELCC Outdoor Spaces

Modifications to the outdoor environment were guided by the Seven Cs design guidelines [40]. A simplified version of the Seven C’s was developed by the research team, as seen in Table 3, in order to facilitate its completion by ELCC staff. At time 1 and time 3, center staff were encouraged to complete the Seven Cs together, centering the perspective of the children at their center. In addition to acting as a baseline measure, the time 1 measurement provided guidance to the centers regarding elements of the outdoor environment that are working well and those that might require improvements. Subsequent measurements indicated how the modifications impacted the quality of the ELCC outdoor spaces.

**Table 3 table3:** Seven Cs characteristics and ratings adapted from Herrington and Lesmeister [40] and Brussoni et al [46].

Characteristic	Rating (5=strongly agree, this is well done in my center; 4=somewhat agree; 3=neutral; 2=somewhat disagree; 1=strongly disagree, this is lacking in my center)
Character	The entire space feels welcoming for the children and ECE (eg, soft materials, dappled light, some color)
Context	The property or area beyond the play space fence contributes positively to the atmosphere of the play space
Connectivity	The children can move seamlessly from one area of the yard to another (eg, defined pathways for tricycles, and pathways for foot traffic only, such as stepping stones or tree cookie paths)
Clarity	Different zones of play are clearly identifiable at the child’s height (eg, messy zones, sand play, water play, tricycle space)
Chance	Throughout the play space, there are natural and loose materials to create and build with, manipulate, and move with
Change	There are ample amounts of natural features, such as trees, shrubs, and groundcovers, in the play space (or directly adjacent to the play space) that change with the seasons
Challenge	The play space encourages different levels of physical and cognitive risk-taking (eg, height, speed, using tools, hiding/getting lost, rough-and-tumble)?

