**Outdoor Space Modification**		
	ELCC centers modify their outdoor space to increase affordances for play. Modifications include adding loose parts, plants, and other natural materials.	Environmental modifications were designed and implemented by each of the ELCC centers, with support from the research team and the Steering Committee. Each participating ELCC center was allocated the same funding to complete environmental modifications and retained considerable discretion in how to allocate these resources. Each center was provided with CAD $8800 (US $6471) for general expenses and CAD $1600 (US $1176) for shade-related components. Liaisons were given a workshop on the Seven Cs design guidelines [40] and provided with a “look-book” with ideas for outdoor space and shade modifications. The research team worked with each center to help support the development and execution of their plans.

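### A higher Seven Cs score at time 3 cannot on its own establish that the modifications improved outdoor-space quality, because unblinded centers rate their own spaces on the framework that guided the changes

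*Protocol article*

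**What the plan says.** The abstract of the protocol article names the quality of the outdoor play space among the secondary outcomes. The section on quality of ELCC outdoor spaces explains how it is obtained:

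- Instrument: "A simplified version of the Seven C’s was developed by the research team". Table 3 shows seven items, each rated from 1 to 5 for agreement.
- Raters and timing: at time 1 and time 3, "center staff were encouraged to complete the Seven Cs together".
- Link to the program: "Modifications to the outdoor environment were guided by the Seven Cs design guidelines", and "the time 1 measurement provided guidance to the centers regarding elements of the outdoor environment that are working well", as well as those that might need improving.
- Interpretation: "Subsequent measurements indicated how the modifications impacted the quality of the ELCC outdoor spaces".

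Table 2 describes the matching program component. "Environmental modifications were designed and implemented by each of the ELCC centers, with support from the research team and the Steering Committee", and "Liaisons were given a workshop on the Seven Cs design guidelines".

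The randomization section says that centers knew their group during baseline data collection and that the five group 2 centers implemented the program after time 2.

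**The concern.** The Seven Cs has two roles. It is part of the intervention, as the framework behind the changes and the source of baseline guidance. It is also the yardstick by which the changes are judged. The judges are staff of the center that made the changes, and they know the center's allocation and what was done. A rise from time 1 to time 3 can reflect a better yard, closer familiarity with the criteria, ownership of the changes, or the expectation that the program should help. The rating cannot separate these.

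At stake is how a secondary outcome is reported. As worded, the article would let a self-rated gain on the program's own guideline be presented as an effect of the modifications on quality.

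**Working it through.** The article states no figure for this outcome, so the check sets its statements side by side.

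1. **Is the outcome framework also an intervention tool?** Yes. The modifications were guided by the Seven Cs, the time 1 rating informed centers about what might need improvement, and Table 2 places a workshop on the guidelines inside the space-modification component. The workshop is stated for liaisons, not for all staff.

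2. **Are the raters independent of the changes?** Not at center level. Table 2 has each center designing and implementing its changes, and the outcome section has center staff doing the rating. No independent or blinded rating of the spaces is described.

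3. **Can a concurrent comparison absorb a rating shift?** No. Ratings are taken at time 1 and time 3 only, and group 2 has had the program by time 3. A between-group comparison at time 3 sets earlier exposure against later exposure, not program against no program. What remains is a before-after change within centers.

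4. **Does the article support the instrument for this use?** It describes the T-TRiPS as validated and reports a κ of 0.82 for the TOPO coding. It reports neither for the simplified Seven Cs. The sources from which Table 3 was adapted are not at hand, so this says what the article reports, not that no validation exists.

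5. **Does the stated interpretation go further than this?** Yes. The sentence in the outcome section reads the later scores as showing what the modifications did to quality.

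**Illustration, on assumptions only.** Suppose true quality does not change, each of the 10 centers gives one mean item score per time point, and ratings shift upward by *b* points. For a two-sided 5% paired t-test, the chance of a significant result is P(|T| > t(0.975, 9)), where T is noncentral t with 9 degrees of freedom and noncentrality *b* × √10 / SD, and SD is that of the change score.

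| Assumed shift *b* | SD 0.5 | SD 0.75 | SD 1.0 |
|---|---|---|---|
| 0.25 | 0.29 | 0.16 | 0.11 |
| 0.5 | 0.80 | 0.47 | 0.29 |
| 1.0 | 1.00 | 0.96 | 0.80 |

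For example, *b* = 0.5 and SD = 0.5 give noncentrality 0.5 × 3.162 / 0.5 = 3.16 and probability 0.80, against a nominal 0.05. Neither the shift nor the SD comes from the documents, one shared score per center is inferred from staff rating together, and the paired t-test stands in for the planned mixed model. The table shows only that a statistically significant rise would not settle the question; it does not estimate the bias.

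**The case against.** The strongest reply is that staff rating was deliberate and explained. The tool was simplified so that staff could complete it, project values guided the data collection methods, and the discussion acknowledges that staff data collection limited what could be gathered. Each center also received CAD $8800 plus CAD $1600 for physical changes, and several items name things that can be seen: loose materials (Chance), trees and shrubs (Change), pathways (Connectivity), distinct zones (Clarity). This stands. A rise is some evidence, and it is legitimate as staff-perceived quality. A reader might infer that the score can show nothing about the yard; the documents do not support that.

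Other stronger readings also fail:

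- *The same individuals designed the changes and scored them.* The overlap is stated only at center level, and Table 2 leaves centers considerable discretion over spending.
- *Regression to the mean will lift the score.* Low items singled out for attention may drift up, but chance-high items drift down. With all seven items scored at every center, picking low items for improvement does not by itself raise the overall mean.
- *The Context item can serve as a negative control.* It asks whether "The property or area beyond the play space fence contributes positively to the atmosphere of the play space". Ownership bias would fall mainly on the features a center changed, so a flat Context score would not rule it out. A redesigned yard could also genuinely alter how the surroundings contribute.
- *The bias has a known size.* Any number of points is an assumption.
- *The measure belongs in process evaluation.* That is a debatable trade-off, particularly after data collection has ended, and the concern does not require it.

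It can also be said that the lack of an unexposed group at time 3 is the more decisive weakness. It does add to the problem. A further rating at time 2 by the same staff would still compare raters who had been through the program with raters who were waiting for it.

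**Conclusion.** The point holds in limited form. On its own, a higher time 3 Seven Cs score cannot establish that the modifications improved outdoor-space quality. It is a valid description of staff-perceived quality and weak evidence of real change. The conclusion rests on the article's own statements about who rates, what guided the changes, when ratings are taken and when group 2 is exposed. It needs no assumption about how large the rating shift is, and the documents give no basis for its size or direction. The reach is modest: one secondary outcome and one over-strong sentence. The video-coded primary outcome is untouched.

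**What to change.** - In the section on quality of ELCC outdoor spaces, replace the sentence on later measurements with wording such as: *time 3 scores describe the before-after change in staff-rated fit with the Seven Cs*.
- In the abstract, label the secondary outcome *staff-rated quality* of the outdoor play space.
- Report the seven items separately, without attributing change causally to the modifications.
- Where a less rater-dependent statement is wanted, report the environmental-interaction codes already part of the video coding done off site. Word it as children's use of loose parts and natural elements, not as yard quality, and note that center liaisons film the videos.

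No new data are needed. The cost is one less favourable effectiveness claim. The codes are also a different construct: they cover loose parts and natural elements but say little about welcome, pathways, zoning or challenge.
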